### Study design

This is a single-center, two-group (1:1), prospective, randomized, double-blind, placebo-control study. The present protocol was designed in accordance with the Standard Protocol Items: Recommendations for Interventional Trials (SPIRIT) guidelines and completed the SPIRIT Checklist [21] (Additional file 1). Additionally, the whole study design is illustrated in Fig. 1 and a SPIRIT figure is presented in Fig. 2.

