### Secondary outcome measures

The following is the secondary outcome:
Gut microbiota abundance and diversity assessed by metagenomic sequencing method.Intestinal permeability determined by the concentration of claudin-3 and LPS.Patient’s characteristic demographic data by investigating and the results of laboratory assessment and the body composition evaluated by anthropometry.Patient’s compliance and adverse effects.

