### Sample size calculation

Based on the previous study results of supplementing synbiotics in NAFLD, this study took the significant reduction of ALT concentration as the main outcome indicator for sample size calculation. According to the research of Eslamparas et al. [23], it was found that the concentration of ALT decreased 11.3 and 4.4 in the intervention and control groups respectively. It aimed to determine an appropriate target sample size that would provide a 90% power (*β* = 0.10) for two-tailed testing with 5% type-1 error rate of the measure. Using the PASS 22.0 software, we calculated a minimum requirement of 42 patients for total. In practice, we decided to enroll a total of 50 participants (*n* = 25 per group), taking into account the 20% drop-out rate before the end of the study.

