### Data analysis

All patients randomized should be included in the analysis and missing data will be handled using multiple imputation. The test data will be analyzed by a statistical expert using SPSS version 22.0 (Chicago, IL, USA). The statistical expert is not involved in the experiment and is only responsible for the analysis of the data. We will use descriptive statistical methods to measure demographics and baseline clinical features. The categorical variables will use the chi-square test or Fisher’s exact test for analysis and are reported as numbers and percentages. The numerical variables will be reported as mean±standard deviation or medians with interquartile ranges (IQR) comparing by Student’s *t* test or the Mann-Whitney *U* test. Ranked data will be analyzed using the rank-sum test. Follow-up data will be compared using the repeated measures analysis of variance (ANOVA). A multiple linear regression method was used to establish a linear equation of multiple linear regression to detect the interaction between the amount of physical activity and the efficacy of LBP supplements.

The alpha and beta diversity of the gut microbiota will be estimated by MOTHUR and QIIME at the OUT level, respectively. Sample cluster will be conducted by QIIME based on UPGMA. KEGG and COG functions will be predicted using the PICRUSt software. Barplot and heatmap of different classification levels will be plotted with T package v3.4.1 and R package “gplots”, respectively. Cases with missing values in the resulting parameters will be excluded from the analysis. All results are statistically significant with *P*<0.05.

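### A flat P<0.05 rule covers all results, including about 29 named secondary measures and microbiota abundance, with no multiplicity control stated

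*Protocol article*

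**What the plan says.** The design has one primary outcome, ALT. Under Sample size calculation it is planned for "two-tailed testing with 5% type-1 error rate of the measure". That is the only comparison for which the article sets a design error rate.

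The secondary list opens with "Gut microbiota abundance and diversity assessed by metagenomic sequencing method". It goes on to claudin-3 and LPS, the laboratory results and body composition as whole blocks, and compliance and adverse effects.

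For the microbiota, Data analysis names diversity estimation, clustering, and barplots and heatmaps at several taxonomic levels. It also states: "KEGG and COG functions will be predicted using the PICRUSt software". It names no test per taxon or per function and does not say how many of either there will be. The same paragraph then ends with the general rule: "All results are statistically significant with" P<0.05. No multiplicity method, ordering of secondary outcomes or exploratory label appears anywhere in the article.

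**The concern.** Read as written, the rule gives any single P value below 0.05 the same standing as the ALT result, wherever it falls among the secondary outcomes. With many outcomes, some will pass by chance.

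This matters because the trial's explanation of benefit depends on secondary results. The Background postulates that LBP helps NAFLD by changing the gut microbiota, and the Discussion expects the trial to clarify mechanism and support microbiota-targeted therapy. That conclusion would rest on outcomes with no stated error control, in a trial of 50 participants.

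**Working it through.** **Starting figure.** The rule's threshold, 0.05, equals the two-sided 5% set for ALT. The planned minimum of 42 patients plays no part in this point. It cannot be reproduced from stated inputs because no standard deviation is given.

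**Step 1: count the named scalar measures.** Blood and stool measures and anthropometry are taken at baseline and week 12, so I assume one between-group test per measure.

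| Group (section) | Measures | Count |
|---|---|---|
| Enzymes besides ALT (Laboratory assessment and imaging) | GGT, AST | 2 |
| Lipids (same) | TG, TC, LDL, HDL, FFA | 5 |
| Inflammatory factors (same) | IL-6, IL-1β, TNF-α, MCP-1 | 4 |
| SCFAs (same) | seven entries, isobutyric acid twice | 6 distinct |
| Steatosis grade (same) | ultrasound | 1 |
| Insulin resistance (Insulin resistance) | insulin, glucose, HOMA-IR | 3 |
| Permeability (Gut microbiota and intestinal permeability) | claudin-3, LPS | 2 |
| Body composition (Clinical evaluation), without height | weight, fat-free weight, BMI, body fat, body fat ratio, waist-hip ratio | 6 |

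Total: 2 + 5 + 4 + 6 + 1 + 3 + 2 + 6 = 29.

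- Low count: omitting insulin resistance and steatosis grade gives 29 − 3 − 1 = 25.
- High count: adding the seventh SCFA entry and height gives 29 + 1 + 1 = 31.
- Not counted: diversity indices, activity questionnaire and tracker data, the unnamed further body measures, and the regression interaction.

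**Step 2: expected false positives if every null is true.** Expected number = m × 0.05. This does not depend on correlation between measures.

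- m = 29: 29 × 0.05 = 1.45
- m = 25: 1.25
- m = 31: 1.55

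**Step 3: chance of at least one.** If independent, it is 1 − 0.95^m.

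- m = 29: 1 − 0.95^29 = 0.774
- m = 25: 0.723
- m = 31: 0.796

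The measures are not independent; HOMA-IR, for example, is calculated from insulin and glucose. A simulation of 29 equally correlated normal test statistics (100,000 replicates, two-sided cut-off 1.96) gave:

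| Pairwise correlation | Chance of at least one |
|---|---|
| 0.3 | 65% |
| 0.5 | 50% |
| 0.7 | 34% |

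**Step 4: the gut-related part of the 29.** The SCFAs (6 or 7 entries) plus claudin-3 and LPS make 8 or 9 measures. Expected false positives are 8 × 0.05 = 0.40 or 9 × 0.05 = 0.45.

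**Step 5: taxa and predicted functions.** The article gives no number, so m is an assumption shown as a range. It is also an assumption that each feature is tested at 0.05.

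| Assumed features | Expected false positives if no effect |
|---|---|
| 20 | 1.0 |
| 50 | 2.5 |
| 60 | 3.0 |
| 100 | 5.0 |
| 1000 | 50 |

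**The case against.** The strongest reply has four parts.

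- **The sentence may only state the conventional threshold.** It does not say unadjusted, and P<0.05 can be applied to adjusted P values. A condensed article commonly leaves such detail to the analysis plan. Part of this stands: had the article been silent, there would be no finding. But it is not silent. It gives one rule for all results, directly after the microbiota methods, and the natural reading is unadjusted.
- **The primary inference is untouched.** This stands in full. There is one primary outcome, tested at 5%, and everything else is already called secondary. Unadjusted secondary outcomes beside a single primary are common practice, so how to treat the remaining scalar outcomes is partly preference.
- **The 77% is an upper-end figure.** This stands, and is why the correlated results are shown. Even at a correlation of 0.7 the chance is about one in three, against a nominal 5%.
- **No per-taxon or per-function testing is written down.** This also stands. Such tests are implied, because abundance is a secondary outcome and the rule covers all results, but they are not specified.

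A reader might therefore infer that several false microbiota findings are to be expected, or that some are near certain. The documents do not support that. The gut-related scalars give fewer than 0.5 expected false positives. Three or more would need about 60 tested features, a number found nowhere in the article, and all of these figures assume no true effect.

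**Conclusion.** The point holds as a fault in a stated rule, not as a forecast of false microbiota results. On the protocol's own list of outcomes, the flat threshold allows about 1.45 chance findings among 29 scalar measures (1.25 to 1.55 across the plausible counts). The chance of at least one lies between about 34% and 77% for correlations from 0.7 down to 0. These figures assume that every null is true, that each measure is tested once, and that P<0.05 means unadjusted.

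For taxa and functions the size is open: 1 to 50 expected false positives for an assumed 20 to 1000 features, if each is tested. The ALT comparison is not affected. The sentence should be changed because the mechanistic conclusion could otherwise rest on chance findings that the plan itself calls significant.

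**What to change.** Replace the closing sentence of Data analysis with a rule along these lines:

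- Two-sided P<0.05 is the confirmatory criterion for the single primary ALT comparison only.
- The false discovery rate is controlled by Benjamini-Hochberg at 5% across all taxa tested, with all taxonomic levels pooled, and separately at 5% across all predicted functions tested.
- The other secondary outcomes, including diversity, are reported as estimates with 95% confidence intervals and labelled supportive or exploratory.

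Pooling the levels prevents selection among nested levels from escaping control. Where no true effect exists and the procedure's usual dependence conditions hold, the chance of any false discovery is at most 5% in each of the two families.

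The cost is a few sentences and a routine calculation, with no new data or visits. The downside is that fewer secondary and microbiota results can be called significant.

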## Discussion

Although witnessed major efforts in the prevention and treatment of NAFLD over the past decades, it remains a worrying disease and prevalent worldwide with the rise of obesity and diabetes [25]. It has been recognized as the most common cause of chronic liver disease and may lead to cirrhosis and liver carcinoma [26]. Noticeably, NAFLD is predicted to be the leading cause of liver transplantation in the next 20 years, contributing to liver-related morbidity and mortality [4]. As of today, despite the tremendous progress made in studying the pathogenesis of NAFLD, the main factors leading to the evolution of NAFLD from simple steatosis (NAFL) to NASH have been largely unknown. However, there is still a lack of approved or effective pharmacological treatment for patients with NAFLD in clinical practice, and lifestyle modifications remain the main strategies [27]. Take the high incidence and serious health risks of NAFLD into consideration, the lack of effective therapy has attracted great concern. Recently, multiple researches have demonstrated that the gut microbiota is closely related to the development and progression of NAFLD through transmitting its own components or metabolites. According to the study of Bäckhed et al. [28], the normal cecum microbiota of conventionally raised mice was colonized into germ-free (GF) C57BL/6 J mice, and it was found that, despite the food intake reduced, the body fat content significantly increased along with insulin resistance occurred after 14 days. Their further research showed that [29], compared with conventional mice with gut microbiota, the GF mice were protected from obesity after eating a Western-style, high-fat, and high-sugar diet. NAFLD could be transmitted to GF mice through fecal microflora transplantation (FMT), which indicates that gut microbes are directly involved in the development of NAFLD. In clinical studies, Miele et al. [30] found that in contrast to healthy volunteers, the intestinal permeability in NAFLD patients was significantly improved, which was related to the increased prevalence of small intestinal bacterial overgrowth (SIBO). These results were consistent with Harte et al. [31], who confirmed that circulating endotoxin levels in NAFLD and NASH patients were higher than in healthy controls. Taken together, gut microbes are considered as the key factor contributing to the development of NAFLD. In view of the results of animal studies and clinical trials, using prebiotics or synbiotics to regulate intestinal flora could become a novel therapeutic target and strategy for the prevention and treatment of NAFLD [32].

At present, there are sparse researches on the application of probiotics in patients with NAFLD. This randomized, double-blind, placebo-controlled study will describe the characteristic of gut microbiota in the progression of NAFLD and the protective effect of LBP supplementation on NAFLD patients. Considering the limited study in this field, the generalization of prebiotics in NAFLD patients still needs high-quality clinical trials to confirm. We believe that the work in this article will help us understand the mechanisms and the therapeutic effects of LBP supplementation on NAFLD. If this treatment proves to be beneficial, it could provide clinical evidence of a potential low-risk treatment option for NAFLD patients and has a significant impact on the gut microbiota targeted therapy for managing NAFLD.

## Trial status

The study is in the patient recruitment phase. This is version 2.0 of the protocol, dated July 30, 2020. Recruitment started in August 2020 and is predicted to end in November 2020.

## Data Availability

After this study is complete, the final trial dataset and statistical codes will be available from the corresponding authors upon reasonable request, except for participants’ personal information. The results will be published in peer-reviewed journals. Findings will be shared with the participants, healthcare workers, the general public, and relevant departments through open-access articles, public talks, conferences, and final reports.

## Abbreviations

NAFLD: Non-alcoholic fatty liver disease
HBV: Hepatitis B virus
HCV: Hepatitis C virus
NASH: Non-alcoholic steatohepatitis
LPS: Lipopolysaccharide
TLR-4: Toll-like receptor 4
FAO/WHO: Food and Agriculture Organization and World Health Organization
LBPs: Lycium barbarum polysaccharides
T2DM: Type 2 diabetes mellitus
SPIRIT: Standard Protocol Items Recommendations for Interventional Trials
GGT: γ-glutamyltransferase
ALT: Alanine aminotransferase
AST: Aspartate aminotransferase
TG: Triglycerides
TC: Total cholesterol
FFA: Free fatty acids
ELISA: Enzyme-linked immunosorbent assays
HOMA-IR: Homeostasis model assessment for insulin resistance
SCFAs: Short chain fatty acids
IPAQ: International Physical Activity Questionnaire-Short Form
ICMJE: International Committee of Medical Journal Editors
DMC: Data Monitoring Committee
ANOVA: Analysis of variance
IQR: Interquartile ranges
NAFL: Simple steatosis
GF: Germ-free
FMT: Fecal microflora transplantation
SIBO: Small intestinal bacterial overgrowth
